**Blinding of participants**

The trial will be presented as study to evaluate the effectiveness of magnetic and copper bracelets on arthritis symptoms. All communication will simply state that one or more of the devices being tested might be intended to act as a placebo.

**Blinding of researcher**

Devices will be independently packaged and sealed within plain white padded boxes by the York Trials Unit. Boxes will simply bear the trial ID number and order of distribution. Devices will then be distributed by the researcher at recruitment and at each follow-up. Each box will contain unique laser labels bearing the trial ID number and the mark of an official stamp. Devices will then be worn for a period of 5 weeks. Participants will be instructed to remove the device immediately before each planned follow-up and to seal the device within the padded box, using the labels provided. Devices will be collected by the researcher at the very end of each visit (i.e. after data collection) and returned to the trials unit. The integrity of each seal will be independently inspected and recorded. Participants will also be instructed in writing to avoid describing the device(s) they have tested in any communication with the researcher. This will help to ensure that researchers remain blind to treatment allocation and that all devices are returned, preventing possible contamination of treatment effects.

**Blinding of health care staff**

GPs, practice nurses and phlebotomists will be provided with similar information about the trial to that given to patients. At no point will they be informed which of the four devices are intended to act as placebos. This will help to maintain blinding amongst participants. Members of staff from participating practices who take part in focus groups before the trial begins will be provided with additional information about the devices involved. These individuals will be asked to refrain from discussing this information with colleagues or patients.

**Stratified random sampling**

Of those practices which express willingness to participate in the trial, nine practices will be selected initially. Ideally three practices will be selected within each trust. This process will be repeated again if necessary in order to include a further three practices. Should the number of potentially eligible patients identified within each practice exceed the target number to be approached (i.e. 24 per practice) by more than 50% (i.e. 36) then patients will be selected at random to receive information about the trial. In such case, patient recruitment will involve stratified sampling according to GP practice. Overall this should help to achieve a fairly representative cross section of patients with RA which will add to the generalisability of findings.

**Wash out-periods**

Whilst randomisation of participants to different allocation sequences should prevent bias associated with potential carry over effects, wash-out periods between treatments will nevertheless be employed. As such, each treatment phase will be separated by a period of one week during which no device will be worn. This should provide additional confidence relating to the internal validity of findings and will aid in the analysis of data (Senn 2002).

- 1. **What are the planned inclusion / exclusion criteria?**

**Inclusion criteria**

- 18 years of age or over
- Diagnosis of rheumatoid arthritis within medical records
- Currently prescribed analgesic medication
- Chronic pain: either persistent or intermittent over a minimum period of three months prior to recruitment (Argoff 2002)
- Current pain: greater than 30/100mm on VAS within the last 24 hours despite medication.

**Exclusion criteria**

- Pregnancy
- Pacemaker or similar device
- Not responsible for administering his/her own medication.
- Dementia or memory impairment, either documented in medical records or if suspected indicated by a score of 6 or below on the Abbreviated Mental Test (Wong et al 2004).
- Diagnosis of malignant disease within medical records
- Forthcoming orthopaedic surgery or analgesic injections within the next 25 weeks.
- Known allergy to copper.
- Regular use of a magnetic or copper bracelet at recruitment
  1. **What is the proposed duration of treatment period?**

Participants begin the first treatment phase immediately after recruitment. Participants will undergo four treatment phases, each lasting five weeks. Each treatment phase will be separated by a one week ‘wash out’ period. Total duration for participation therefore will be 23 weeks.

- 1. **What is the proposed frequency and duration of follow up?**

Baseline questionnaire data will be collected at recruitment. Participants will then be followed up on four further occasions, separated by intervals of six weeks. These will occur at the end of each treatment phase. Blood samples should be taken within a two day period either side of each planned follow-up.

- 1. **What are the proposed outcome measures?**

The recommended approach for assessment of outcomes in clinical trials of treatments for RA is to examine change according to a ‘core set’ of disease activity measures defined by the American College of Rheumatology (ACR). This consists of seven measures. Three of these are self report measures; pain, physical function and global assessment of disease activity. Three rely on clinical examination; swollen joint count, tender joint count and professional assessment of disease activity. With the final measure involving serum analysis of acute phase reactants. (Arnett et al 1988, Felson et al 1993, Felson et al 1995, Rindfleisch and Muller 2005).

For the proposed trial three of these measures would require repeated physical assessment by a suitably qualified clinician, generally speaking a rheumatologist. However this is neither feasible nor warranted. Indeed, Pincus (2005) has shown that a pooled index of the three self-report measures may discriminate equally well to the ‘core set’ in terms evaluating the efficacy of treatments in placebo controlled trials. Perhaps more importantly however the primary focus of this trial is on the effects of magnet therapy on pain and inflammation in RA rather than overall disease activity. As such, the primary outcome measure should be pain specific.

For the present trial a 100mm pain visual analogue scale (VAS) was selected, as consistent with the recommended method of pain measurement according to ACR criteria. This displays verbal anchors indicating “no pain” at one end to “worst pain ever” at the other. Visual analogue scales have been widely used for quantifying pain for a range of conditions including rheumatoid arthritis and have been shown to be adequate for this purpose in terms of reliability, validity and sensitivity (Malaise and Franchimont 1987, Duncan 1989, Bellamy et al 1999). The McGill Pain Questionnaire will be used as a second pain outcome measure, as this covers affective components and may also be used to validate findings from the VAS. This will also aid comparison of findings with studies reported elsewhere.

Possible variation in participants’ use of medication may have a confounding effect on pain outcomes. This will have the tendency of reducing any otherwise observable difference between groups resulting from a true treatment effect. Medication use during each treatment phase will therefore be quantified. This will enable pain outcomes to be adjusted if necessary on the basis of regression analysis. Whilst the main emphasis will be placed on measuring changes in the use of prescribed analgesic drugs (e.g. co-codamol and paracetamol), it is important to note that use of other drug types (e.g. NSAIDs) will have an impact on pain and therefore will be accounted for also.

Mechanisms involved in the alleviation of pain in RA include reduction in inflammation of the synovium. Widely used surrogate measures of inflammation include blood tests, typically C-reactive protein (CRP) and erythrocyte sedimentation rate (ESR). These are referred to by the ACR as acute phase reactants. Together these represent favoured outcome measures for monitoring disease activity (Felson et al 1995). Results presented by Segal and colleagues (2001) appear to show that ESR may show slightly greater variability and therefore discriminative power in terms of detecting treatment effects. However plasma viscosity (PV) has now replaced ESR within the local region of this trial. Given limitations associated with the sensitivity and specificity of individual tests, both ESR and CRP tests will be conducted as proxies for inflammation within the proposed trial.

The possibility that magnet therapy may alleviate pain in chronic musculoskeletal conditions via endogenous opiod channels has also been considered. However the decision has been made not use blood samples for the purpose of exploring changes in endogenous opiods, such as beta-endorphin. This is due a number of factors, including the fact that endorphin tests are not routinely used within the NHS and therefore costs are likely to be prohibiting. Moreover, the requirement for additional blood samples involving non-routine tests is unlikely to be viewed as acceptable by research participants.

Additional disease specific outcome measures will consist of Patients’ Assessment of Physical Function and Subjects Global Assessment of Disease Activity (S-GADA) (Arnett et al 1988, Hochberg et al 1992, Felson et al 1993). Data provided by these instruments will be pooled together with other data to provide an overall index of disease activity (Pincus 2005).

Generic outcome measures will consist of the SF-36 and EuroQol. For the proposed trial these represent valid outcome measures in their own right and will also aid comparison of findings with other studies, such as MACROPOD. Participants will also be asked to report on their use of health care resources and personal expenditure relating to health care. This together with data collected using the EuroQol will facilitate any cost-effectiveness analysis of magnet therapy arising from this trail (EuroQol Group 1990).

Participants will be asked to report on compliance in terms of time spent wearing each device. This may related to treatment effectiveness and assurance will be required that participants actually wore the devices they were given. However poor compliance will not be used as a basis for exclusion from analyses. Success of blinding will be assessed by asking participants to judge whether or not each device worn was a placebo. Adverse events and reactions will be monitored throughout the trial.

**How will the outcome measures be measured at follow-up?**

**Questionnaire**

Questionnaires will be sent to participants two to three days before each planned follow up. Completed questionnaires will then collected by the chief investigator. These will contain all self-report outcome measures described previously.

**Pill Count**

Participants will be visited at home by the chief investigator at recruitment and at the end of each treatment phase. With the participants help and prior consent (obtained at recruitment) a ‘pill count’ will then be conducted. This will involve counting the remaining number of tablets or capsules that the participant has in their possession for each analgesic, NSAID or DMARD received on repeat prescription. Issue dates will also be recorded. At a later stage prescription records will be obtained from each participant’s general practice. Together this information will be used to estimate use of prescription medication during each treatment phase. This approach has been used successfully by both the RESPECT trial (Wong et al 2004) and the MACROPOD trial. Before this, participants will also be asked to estimate the extent to which their medication use altered during each phase, using a 5-point Likert scale. This questionnaire item will be used for the purpose of validating estimated medication use.

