A search of The Cochrane Central Register of Controlled Trials (CENTRAL) and the *meta*Register of Controlled Trials (*m*RCT) revealed no RCTs of magnet therapy for arthritis currently in progress, apart from that of the MACROPOD trial.

MACROPOD (ISRCTN 18518978) is a randomised double-blind placebo controlled crossover trial of magnet therapy for pain relief in osteoarthritis, which is currently at the analysis stage. In total 45 participants were randomly allocated to one of four treatment sequences consisting of four phases, with each phase lasting one month. Participants each wore a MagnaMaxTM bipolar bracelet (mean strength 200.9mT, SD 17.7), an attenuated MagnaMaxTM (45.3mT, SD 12.0), a non-magnetic MagnaMaxTM and a copper bracelet. Outcomes measures included a 10cm pain visual analogue scale, WOMAC, McGill Pain Questionnaire, SF-36, EQ-5D together with economic items. Medication use was measured by triangulation of diary records, prescription records and by manually counting remaining tablets and capsules before and after each phase. Whilst originally developed as a pilot study for future trials of magnet therapy, MACROPOD is nevertheless fully powered for the purpose of demonstrating a meaningful clinical difference between the commercially available PSMD employed and the three ‘placebo’ devices in terms of the primary outcome. Findings from this study are due to be published towards the end of 2006.

- 1. **How will the results of the trial be used?**

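### Tablets are counted only at recruitment and at phase ends, so the medication estimate for phases 2 to 4 includes the device-free wash-out week and spans 42 days against 35 in phase 1

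*Protocol*

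**What the plan says.** **Counting.** The Pill Count section of the Protocol states: "Participants will be visited at home by the chief investigator at recruitment and at the end of each treatment phase". The counts are combined with issue dates and prescription records, and the purpose is given as: "Together this information will be used to estimate use of prescription medication during each treatment phase".

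**Schedule.** The section on duration of the treatment period says "Participants begin the first treatment phase immediately after recruitment" and "Participants will undergo four treatment phases, each lasting five weeks". The Wash out-periods section says "each treatment phase will be separated by a period of one week during which no device will be worn". On follow-up, the Protocol says "Participants will then be followed up on four further occasions, separated by intervals of six weeks" and "These will occur at the end of each treatment phase". Appendix 1 places the phases at weeks 1–5, 7–11, 13–17 and 19–23.

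**Device hand-over.** Under Blinding of researcher, the next device is given out at the follow-up that closes the previous phase. No visit, and so no count, falls on the day when device 2, 3 or 4 is first put on.

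**Use of the measure.** Analgesic use is a listed secondary outcome. The planned analyses adjust the treatment effects for medication use as a secondary step, and mention period adjustment only as a possibility. Under the economic heading, a reduction in medication use is enough by itself to start a cost-effectiveness analysis.

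**The concern.** The stated target is medication use in each treatment phase. The two counts that bracket phases 2, 3 and 4 also enclose the wash-out week before the phase. Tablets taken without a device therefore cannot be told apart from tablets taken on it. Prescription records and issue dates show supply, and the five-point item shows only perceived change. The Protocol states no diary or other means of separating that week.

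Two things are at stake. The time base differs between phase 1 and the later phases. The figure credited to a device also contains a week in which it was not worn, and in which use may still reflect the previous device. The Protocol itself expects changes in medication to mask a true effect on pain, so the quality of this measure matters for the adjusted analysis as well as for the secondary outcome.

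**Working it through.** **1. Reproduce the Protocol's calendar.** Four phases of 5 weeks and three wash-outs of 1 week: 4 × 5 + 3 × 1 = 23 weeks. This agrees with the stated total, and 5 + 1 = 6 weeks agrees with the stated follow-up interval.

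**2. Intervals between counts.** Counts fall at recruitment (week 0) and at the end of weeks 5, 11, 17 and 23.

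| Phase | Count to count | Days | Wash-out days included |
|---|---|---|---|
| 1 | week 0 to 5 | 35 | 0 |
| 2 | week 5 to 11 | 42 | 7 |
| 3 | week 11 to 17 | 42 | 7 |
| 4 | week 17 to 23 | 42 | 7 |

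Sum: 35 + 3 × 42 = 161 days = 23 weeks. Off-device share in phases 2 to 4: 7/42 = 16.7%.

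**3. Effect by scale.** Let d be daily use on a device and w daily use in the wash-out, with w not depending on the device.

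*Raw total.* Phase 1 gives 35d, and phases 2 to 4 give 35d + 7w.
- At constant use (d = w) the ratio is 42/35 = 1.20, so later totals are 20% higher.
- The contrast of devices A and B within any phase is 35(dA − dB). The term 7w cancels, leaving a period shift plus noise and no dilution in tablets.

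*Daily rate over the full interval.* Phase 1 gives d, and phases 2 to 4 give (35d + 7w)/42 = (5/6)d + (1/6)w.
- At d = w the step between phases disappears.
- The contrast in phases 2 to 4 is (5/6)(dA − dB), a loss of one sixth.
- Averaged over four phases: (1 + 3 × 5/6)/4 = 0.875, a loss of 12.5%.

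**4. Illustration (assumption, not a Protocol figure).** Suppose a device cuts daily use by 20% and use returns to its off-device level in the wash-out. With off-device use set to 1 per day, the 42-day measure is (35 × 0.8 + 7 × 1)/42 = 35/42 = 0.833, an apparent cut of 16.7%. For assumed true cuts of 10% and 30% the apparent cuts are 8.3% and 25%. A percentage contrast built on raw 42-day totals is diluted in the same way.

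**5. Carry-over.** If w depends on the previous device, the term 7w no longer cancels, and part of that device's effect is booked to the next one. This holds on both scales. The Protocol gives no figure for how fast use returns to its off-device level, so I put no number on it.

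**6. What a start count would do.** Counts at the end of weeks 6, 12 and 18 as well would give 35 device-on days in every phase.

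**The case against.** **This is matter for the analysis plan.** The Protocol does not say that raw totals will be compared, and scaling to days is ordinary SAP content. That stands for the 20% step. It does not stand for the off-device sixth: no later formula can remove tablets that were never counted separately.

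**Randomisation balances it.** Allocation over all 24 sequences puts each device in phase 1 equally often in expectation, so this is not a systematic bias for or against any device. A reader might infer such a bias, and the documents do not support it. Balance is only in expectation: the Protocol calls blocking unnecessary. With 69 participants, the number starting on a given device has mean 69/4 = 17.25 and SD √(69 × 0.25 × 0.75) = 3.6. Period adjustment is not firmly planned.

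**Inflation and dilution together.** A reader might add the 20% and the 12.5%. For an absolute contrast they belong to different definitions of the outcome and do not both apply.

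**The pilot counted differently.** The Protocol says its approach was used in the pilot crossover trial, and describes that trial as "manually counting remaining tablets and capsules before and after each phase". A reader might infer a different count schedule. The documents do not show one. The pilot had four one-month phases within 16 weeks of participation, which appears to leave no room for wash-outs. With back-to-back phases, the count after one phase is the count before the next, so the description fits the same visit pattern. What appears to differ is that this trial has inserted wash-out weeks between the visits.

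**It is secondary.** Agreed. The critical test is the unadjusted comparison of pain VAS, which uses no pill count.

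**Conclusion.** The point holds as a modest measurement gap. On the planned schedule, the estimate for phases 2 to 4 covers 42 days, of which 7 (16.7%) are off-device, and nothing stated in the Protocol separates them. The consequence is one of two, depending on the scale:
- a 20% period step in raw totals at constant use, with the absolute device contrast intact;
- a contrast reduced to 5/6 in phases 2 to 4 (12.5% lost over four phases) for daily rates over the full interval.

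Possible carry-over from the previous device comes on top in either case.

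These sizes assume visits on the planned days and, except for carry-over, wash-out use that does not depend on the device. The four-phase average also assumes that each device is spread evenly over the phases. The finding concerns a secondary outcome, the medication-adjusted analysis and the trigger for the economic analysis. It gives no ground for doubting the primary unadjusted VAS test.

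**What to change.** **Data collection.** Put a card in each sealed box. On the day the device is first put on, the participant writes the date and the remaining tablets of each listed drug, and returns the card in the box. Include a card in phase 1 alongside the researcher's count. The start-count method is then the same in all phases, and the participants' counting can be checked against the researcher's. The card should ask nothing about the device, so blinding is unaffected.

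**Outcome and model.** Define medication use as mean daily use over device-on days, from start count to end count and allowing for issues in the prescription records. Commit to period in the model for this outcome.

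**Missing start counts.** Use the total over the whole interval with period in the model, or a daily rate reported as diluted by the wash-out week. Choose one in advance and do not mix the two scales in one analysis.

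**Cost.** One printed card per box (69 × 4 = 276 cards), a sentence in the Pill Count section and a few lines of analysis wording. No visits are added. The drawbacks are that start counts are self-reported and that participants have one more small task.

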**Blood tests**

Participant consent will be required to provide blood samples on five separate occasions, i.e. shortly after recruitment and at each follow up. Blood samples will be taken by a phlebotomist, practice nurse or GP. Samples will be sent via normal NHS channels to local haematology laboratories for PV and CRP testing. Results will be entered into the patient’s medical records and collected for the trial at a later date. Once recruited, all participants will be followed up regardless of any failure to provide blood samples.

**Case Report Forms**

General practices will be encouraged to report all adverse events or reactions using standard forms provided. Similarly, participants will be asked to report any such events directly to the trial and inform their GP.

- 1. **What is the proposed sample size?**

The sample size for this trial was determined using *GPower* (Erdfelder et al). This suggested that complete data from 62 participants would provide 80% power to detect a minimal clinically important improvement of 20% in pain outcomes (Felson et al 1995) for the full strength device using a one way analysis of variance (P = 0.05). This assumed a mean score of 65 on a standard 100mm pain visual analogue scale (VAS) for the demagnetised device, with a difference of -13 for the full strength device and -6.5 for each of the placebo devices. An upper limit of 21.7mm was set for the common standard deviation within subjects. Estimates for both mean and standard deviation were based on data obtained by the MACROPOD trial, together with data presented by Segal and colleagues (2001).

Allowing for a maximum of 10% attrition from recruitment to final data collection, 69 participants will need to be recruited (refer to Section 3.12).

- 1. **What is the planned recruitment rate?**

216 potentially eligible patients with RA will be approached with information about the trial and invited to take part. Based on experience from the MACROPOD trial and taking into account the fact that blood samples will be required for participation, it is anticipated that roughly 50% (108) of patients will fail to respond.

For those who express an interest, a meeting will then be arranged. Patients will be sent an appointment letter together with a copy of the consent form and a baseline questionnaire. During the meeting the chief investigator will offer a detailed explanation of the trial, show examples of the devices involved and answer any questions. He will then assess eligibility, seek the patients’ written consent to participate in the trial and collect the baseline questionnaire. Meetings will normally take place within the patient’s home as a pill count will also be conducted if the person is recruited. At this stage it is estimated that up to 35% (38) patients will either be found to be ineligible or decline to participate. This should leave 69 patients who will then be entered into the trial.

Provided that an efficient method of arranging appointments is organised, either by means of secretarial support or by allowing approximately 4 weeks to field calls, then the actual period required for visiting and recruiting all participants should take no longer than 8 weeks in total. This assumes a figure of between 2 to 3 appointments per day, allowing for gaps in appointments and time spent on additional tasks, such as organising blood tests.

- 1. **Are there likely to be any problems with compliance?**

Non-compliance in terms of failure to wear devices for the recommended minimum of 12 hours per day is unlikely to represent a major problem. Compliance will be measured and systematic bias should be avoided due to the random allocation of participants to different intervention sequences. Whilst the present study employs placebo-control, the emphasis is nevertheless that of a pragmatic evaluation of the therapeutic effectiveness of magnet therapy within a real world setting (Schwartz and Lellouch 1967). Non-compliance therefore represents a valid outcome in its own right.

- 1. **What is the likely rate of loss to follow-up?**

It is anticipated that loss to follow-up should not exceed 10%. In relation to this figure it is worthwhile noting that just 1 participant out of 45 (2%) withdrew from the MACROPOD trial. However the duration for participation (16 weeks) was shorter than the proposed trial. More importantly, participants in the CAMBRA trial will be asked to provide blood samples on successive occasions. This may serve as a disincentive for continued participation. Efforts will be made however to continue follow up for participants who refuse to provide further blood samples.

- 1. **How many centres will be involved?**

Up to 12 general practices will be recruited in two phases. Initially the trial will seek to recruit nine large general practices over a period of one month from three primary care trusts: 1) Hull PCT; 2) East Riding of Yorkshire PCT; 3) Selby & York PCT. Practices approached will be those with four or more partners. This will help to ensure the availability of a practice nurse or phlebotomist at each site for the purpose of taking blood samples. Roughly equal numbers of patients with RA will then be contacted by each practice to help achieve a fairly representative sociodemographic cross section of this clinical population. Should the nine practices fail to identify a sufficiently large number of patients with RA, then an additional three practices will be recruited.

- 1. **Give details of the planned analyses**

Data from all participants recruited into the trial will be included in the analysis according to intention to treat. The basic statistical method used for the purpose of primary analysis will be that of analysis of variance. This will look for a significant difference in treatment outcomes amongst the four devices using follow up scores from each treatment phase. If magnet therapy of any true therapeutic benefit one would expect this to show a statistically significant difference between devices in favour of better outcomes for the experimental (full strength MagnaMax) device. However if a significant difference is observed with poorer outcomes for the demagnetised dummy device then the other three devices, then this would tend to indicate that any benefit of magnet therapy may be attributed simply to a placebo effect. This assumes that both attenuated and copper bracelets serve as valid placebos, which is an issue that will be explored in greater detail. Within this analysis a significant difference in treatment effects for the pain VAS (as the primary outcome measure) will be viewed as the critical test.

As a secondary step in the analysis, estimated treatment effects for each of the devices will also be adjusted according to medication use and compliance, for both of which continuous data will be available. The assumption here is that both of these variables are likely to modify the effects of treatment in terms of all major outcomes. Specifically it is believed that a reduction in either of these variables is likely to reduce the apparent effectiveness of magnet therapy. In pragmatic terms this may not be important, however for the majority of readers this may be interest. The basic approach used for this purpose will be that of multiple regression, testing first for non-linear relationships (Bland 2000).

Further refinement to analysis plan will be sought towards completion of the data collection stage of this trial. This will take into consideration advice from [name] and may involve adjusting for possible period effects as described using a ‘basic estimators approach’ outline in Section 5.4.1 of *Crossover Trials in Clinical Research 2ed* (Senn 2002)

Treatment effect estimates will be presented for each of the four devices together with their standard error and 95% confidence intervals. The computer package used for this purpose will be SPSS® and possibly also SAS®.

- 1. **Are there any planned subgroup analyses?**

Further analyses will be performed in order compare effects according to age, sex and primary location of pain. Differences in effect according to treatment preference will also be explored. The focus here will be on identifying possible baseline variables which may serve as useful predictors of treatment effectiveness, although dangers associated with multiple testing will be acknowledged. Similarly, this trial will explore a number of factors in terms of their possible role in mediating observed placebo effects. These will include level of education, belief in holistic and complementary medicine and belief in the paranormal. The latter of which will be measured at baseline using the HCAMQ (Hyland et al 2003) and Australian Sheep-Goat Scale (Thalbourne 2001).

- 1. **What is the proposed frequency of analyses?**

Analysis will be performed at the end of the trial only, although adverse events and reactions will be actively monitored.

- 1. **Will the trial address any economic issues?**

Quality of life, medication use and data relating to health care expenditure will be collected as part of the trial. If magnet therapy is shown to be effective for reducing either arthritis symptoms or medication use then a cost-effectiveness analysis will be conducted. This will be lead by staff from the Centre for Health Economics at The University of York.

- 1. **What is the estimated research cost for the trial?**

Total: £13,635 excluding salaries. This is based on: £6900 in order to reimburse general practices (see below); £2000 for research travel expenses; £1800 for device costs; £1035 for trial participant expenses; £1000 printing and administration; £500 focus group expenses; £400 telephone charges.

- 1. **What will be the NHS cost implications for the trial?**

The trial will reimburse general practices for costs incurred in supporting this trial. This relates to time of nurses, phlebotomists, clerical staff and GPs in performing research activities which place a strain on resources. Activities include identifying / contacting patients as part of recruitment. Clerical staff will also book and accommodate participant appointments. Blood samples will be taken from each participant on a maximum of four occasions. In each case this will involve two samples. In total, general practices will be reimbursed up to £100 per participant. Payments will be issued on the basis of £25 per visit. This assumes haematology charges of £10.15 for CRP, £6 for PV and £8.50 for staff time. This amounts to a maximum of £6900, although the actual figure is likely to be lower as some participants will fail to provide a complete set of blood samples.

- 1. **Over what period is funding requested?**

N/A

- 1. **Is a pilot feasibility stage planned?**

A pilot study has already been conducted in order to test several methodological features of the proposed trial, i.e. MACROPOD.

Before patient recruitment begins, two focus groups will be formed.One involving GPs, practice nurses and phlebotomists. Members of this group will be drawn from practices which express an interest in participating in CAMBRA. The other will consist of people with RA and those involved in providing direct support to people with RA. These will be drawn from members of community support groups for people with affected by RA and not via NHS channels.

Each focus group will be provided with a detailed outline for the proposed trial, together with trial materials in advance. Feedback will be sought on a variety of issues, including possible weaknesses with trial methodology and suitability of written material. The groups will help to identify any special considerations associated with the study of rheumatoid arthritis which may have been overlooked. Each group will also discuss issues specific to the use of blood tests, such as their acceptability to study volunteers. Information gathered will be used to refine the trial protocol. This may result in an application for the approval of minor amendments from local research ethics committee concerned.

1. **DETAILS OF THE TRIAL TEAM**
   1. **Trial management**

The Department of Health Sciences at The University of York will act as the co-ordinating centre for CAMBRA. This trial will be led by [name] as the chief investigator, who will be responsible for clinical and scientific co-ordination, together with day to day management. This will include recruitment of all general practices and participants, data collection, analysis and dissemination of findings. [name], as Director of the York Trials Unit will be responsible for supervising patient randomisation and data management. He will also act as an advisor on matters relating to trial design and methodology. [name] will act advisor on matters concerning the use and evaluation of complementary and alternative medicine. [name] will serve as a statistical advisor to the trial. [name] from The University of Hull will advise on matter concerning general medical practice. As a co-investigator for MACROPOD, he will also contribute towards the evaluation of this trial. For the purpose of trial development further support will be sought from a leading rheumatologist.

- 1. **Participating centres**

Either nine or twelve general practices will be recruited across three PCT regions. Practice managers / practice staff will identify potentially eligible patients from medical records with support from the chief investigator. Honorary contracts will be obtained for the chief investigator for each of the PCTs involved. Administrative staff from each practice will then contact patients by post. Each patient will be sent an information sheet, letter of invite to participate and a standard covering letter expressing support for the trial, signed by one of the GPs. Patients will be asked to contact the chief investigator if they are interested in participation.

General practice will be informed when a patient is recruited into the trial. A series of four appointments will then be made for blood samples to be taken from the participant by either a nurse or a phlebotomist located within the practice. Administrative staff will be responsible for organising these appointments, sending samples for analysis and providing the trial with the results. Following all other data collection activities, each practice will be visited by the chief investigator during which prescription histories and blood tests results will be obtained.

1. **APPENDICES**
   1. **Appendix 1: Randomisation sequence for device allocation**

|  | | **Order of treatment phases (weeks)** | | | | | | | |
| --- | --- | --- | --- | --- | --- | --- | --- | --- | --- |
| **wk1** | **weeks**  **1 to 5** | **wk6** | **weeks**  **7 to 11** | **wk12** | **weeks**  **13 to 17** | **wk**  **18** | **weeks**  **19 to 23** |
| **Sequence Number** | **1** | Recruitment | *Full Strength* | wash out | *Attenuated* | wash out | *Demagnetised* | wash out | *Copper* |
| **2** | *Full Strength* | *Attenuated* | *Copper* | *Demagnetised* |
| **3** | *Full Strength* | *Demagnetised* | *Attenuated* | *Copper* |
| **4** | *Full Strength* | *Demagnetised* | *Copper* | *Attenuated* |
| **5** | *Full Strength* | *Copper* | *Attenuated* | *Demagnetised* |
| **6** | *Full Strength* | *Copper* | *Demagnetised* | *Attenuated* |
| **7** | *Attenuated* | *Full Strength* | *Demagnetised* | *Copper* |
| **8** | *Attenuated* | *Full Strength* | *Copper* | *Demagnetised* |
| **9** | *Attenuated* | *Demagnetised* | *Full Strength* | *Copper* |
| **10** | *Attenuated* | *Demagnetised* | *Copper* | *Full strength* |
| **11** | *Attenuated* | *Copper* | *Full Strength* | *Demagnetised* |
| **12** | *Attenuated* | *Copper* | *Demagnetised* | *Full Strength* |
| **13** | *Demagnetised* | *Full Strength* | *Attenuated* | *Copper* |
| **14** | *Demagnetised* | *Full Strength* | *Copper* | *Attenuated* |
| **15** | *Demagnetised* | *Attenuated* | *Full Strength* | *Copper* |
| **16** | *Demagnetised* | *Attenuated* | *Copper* | *Full strength* |
| **17** | *Demagnetised* | *Copper* | *Full Strength* | *Attenuated* |
| **18** | *Demagnetised* | *Copper* | *Attenuated* | *Full Strength* |
| **19** | *Copper* | *Full Strength* | *Attenuated* | *Demagnetised* |
| **20** | *Copper* | *Full Strength* | *Demagnetised* | *Attenuated* |
| **21** | *Copper* | *Attenuated* | *Full Strength* | *Demagnetised* |
| **22** | *Copper* | *Attenuated* | *Demagnetised* | *Full Strength* |
| **23** | *Copper* | *Demagnetised* | *Full Strength* | *Attenuated* |
| **24** | *Copper* | *Demagnetised* | *Attenuated* | *Full Strength* |

- 1. **Appendix 2: Participant flow – illustration of CONSORT diagram**

